### Informed consent

All eligible participants will receive detailed verbal and written information about the study objectives, procedures, potential risks and benefits, and their right to withdraw at any time without penalty. Written informed consent will be obtained from all participants before enrollment. All procedures involving participants in this study will follow the guidelines of the Research Ethics Committee of Bu-Ali Sina University (IR.BASU.REC.1402.076) and adhere to the 2013 Declaration of Helsinki.

### Qualifications of intervention providers

The intervention will be overseen by a PhD-level sports rehabilitation specialist with expertise in sports training, who will explain the study’s objectives to coaches and athletes, obtain informed consent, and supervise all assessments in the Sports Rehabilitation Laboratory at Bu-Ali Sina University. Day-to-day implementation of the training program will be conducted by trained team coaches under the supervision of the research team.

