### Maintenance strategy

Several strategies will be used to minimize participant dropout. A study coordinator will send reminder text messages before each scheduled training and assessment session. Training sessions will be embedded within each team’s existing practice schedule to minimize scheduling conflicts with competitions and academic commitments. Where feasible, makeup sessions will be offered for absences due to illness or minor scheduling conflicts, provided the participant does not meet the withdrawal threshold defined in the Exclusion Criteria. Reasons for dropout or withdrawal will be systematically recorded and reported using a CONSORT flow diagram. Participants who complete the full protocol will receive individualized feedback on their landing mechanics as a non-monetary incentive to continue engaging.

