Athletes will progress to the next training phase only when they consistently meet predefined progression criteria across three consecutive sessions. Movement quality will be assessed by a trained coach using a standardized checklist, ensuring appropriate lower-extremity alignment according to predefined movement-quality criteria. Cognitive performance will also be evaluated, requiring athletes to commit no more than three predefined cognitive errors per session during tasks involving stimulus responses or rule-based challenges. Athletes must maintain movement quality under dual-task conditions without clinically meaningful deterioration compared with single-task performance and execute tasks at the prescribed speed and intensity while meeting cognitive demands. Since progression is individualized, athletes who do not meet the criteria after completing the planned two-week phase will remain at the same level with modified or alternative exercises of similar complexity until the requirements are achieved, thereby supporting adequate motor learning, confidence development, and minimizing inappropriate progression-related injury risk. All progression decisions will be documented using standardized forms and reviewed weekly by the supervising sports rehabilitation specialist to ensure safety.

Training intensity will be indirectly quantified using the session rating of perceived exertion (session-RPE) method [23]. Approximately 30 minutes after each session, each participant will rate her perceived exertion using the modified Borg CR-10 scale; session-RPE will then be multiplied by session duration (minutes) to calculate session training load. Weekly training load will be reviewed by the supervising sports rehabilitation specialist alongside the movement-quality and cognitive-error checklists to identify unusual increases in perceived exertion and inform individualized progression decisions.

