### Implementation

An independent investigator, not involved in participant recruitment, assessment, or intervention administration, will generate the randomization sequence and maintain exclusive access to the randomization list. After confirming eligibility and obtaining informed consent, this investigator will randomize participants. The study coordinator, blinded to group assignment, will enroll eligible female volleyball athletes with DKV and schedule assessments. Due to the nature of the intervention, trainers cannot be blinded to group allocation. The allocation process is designed to minimize selection and performance bias throughout the study.

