### Assignment of interventions: Blinding

This study will be conducted as a participant- and assessor-blinded randomized controlled trial. Participants will be informed that they are receiving training, but will not know whether the program includes neuromuscular training with or without cognitive components. Given the structural similarity between protocols, participants may be unlikely to determine their group assignment. To minimize communication between groups, intervention and control sessions will be scheduled on separate training days. Outcome assessors will remain blinded to group assignments. Participants will be instructed not to disclose intervention-related information during evaluations.

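### The trial is labelled participant- and assessor-blinded, but the specialist overseeing training also supervises every outcome assessment, and participants perform the very content they are said not to know

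*Protocol article*

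**What the plan says.** The section Assignment of interventions: Blinding states: "This study will be conducted as a participant- and assessor-blinded randomized controlled trial". It adds: "Outcome assessors will remain blinded to group assignments". Of participants, it says that they "will not know whether the program includes neuromuscular training with or without cognitive components", and it gives the structural similarity of the two programs as the reason they may not work out their group. The Discussion lists blinded assessors as a protection against observer bias.

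Qualifications of intervention providers gives one PhD-level sports rehabilitation specialist several roles. This person oversees the intervention, explains the objectives to coaches and athletes, and is to "obtain informed consent, and supervise all assessments in the Sports Rehabilitation Laboratory".

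Under Intervention protocol, in the paragraphs on progression that follow Table 2, progression decisions are to be "reviewed weekly by the supervising sports rehabilitation specialist to ensure safety". The same specialist reviews weekly training load together with the movement-quality and cognitive-error checklists.

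Control group protocol gives the control arm the same exercises with every cognitive challenge removed. Under Implementation, only trainers are said to be impossible to blind.

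**The concern.** A blinding claim tells readers which sources of bias they may set aside. Here the article gives one person both knowledge of the arm and authority over the outcome session, while stating that assessors are blinded. It also claims that participants will not know a fact about their own training that they meet at session after session.

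The exposure falls on the post-test. Envelopes are opened only after baseline testing (Concealment mechanism), so baseline values are protected. The primary analysis is the group-by-time interaction, so anything that shifts post-test values in one arm only goes directly into the effect estimate. Several measures depend on the tester or on effort: the decision that a landing is invalid, hand-held dynamometry and goniometer readings. The SF-12 is self-reported.

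**Working it through.** No figure in the article bears on this point, so the check sets its statements side by side.

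**Assessor blinding**

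1. *Does the overseeing specialist know the arm?* The weekly review covers cognitive-error checklists. Cognitive tasks exist as a program component only in the experimental arm, so those records identify it. That the specialist under Qualifications of intervention providers and the one under Intervention protocol are the same person is inferred from matching title and supervisory role. No other such specialist is described. Even without this inference, overseeing both programs gives knowledge of who is in which.
2. *Is that person present at outcome testing?* Yes, as supervisor of all assessments.
3. *Does any other statement separate the roles?* Data management names two trained sports rehabilitation specialists who collect and enter data, but does not say that they are distinct from the overseeing specialist or have no part in training. The separation statement there follows the sentence on data quality control and most naturally covers the data management and analysis team. It does not reach the testing session.
4. *Is there a route to the primary outcome?* Data collection methods plans three landings with and three without cognitive load. A landing with loss of balance or control is to be judged invalid and left out of the analysis. Some of the examples are plainly observable, such as stepping outside the target, but loss of postural stability needs judgement. The article does not say whether a discarded landing is repeated. If it is not, one such call removes 1 of 3, a third of that participant's data for the condition.

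**Participant blinding**

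1. The fact participants are said not to know is whether their program has cognitive components.
2. In Table 2, week 1 consists of attention to alignment and technique, so it may look alike in both arms. From week 2 almost every exercise carries an overt task, and over the eight weeks these include arithmetic, Stroop naming, number recall and reversed directional cues, with a partner giving prompts.
3. At three sessions a week for eight weeks there are 3 × 8 = 24 sessions. Leaving out week 1, 24 − 3 = 21 sessions in the experimental arm contain overt cognitive tasks on the planned schedule.
4. The control arm has none in any session.

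What participants are said not to know is therefore what they do, or do not do, at training. Separating the arms ("intervention and control sessions will be scheduled on separate training days") limits comparison between athletes but does not hide from an athlete the content of her own session.

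**The case against.** The strongest reply is that supervising is not assessing. No sentence has the overseeing specialist score a landing, hold the dynamometer or read the goniometer, and the article says outright that assessors stay blinded. Both statements can be true together. This stands: the document does not show that raters are unblinded. It shows that the stated roles do not secure the claim.

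On participants, both arms meet cognitive tasks at screening and testing, so a control athlete may not realise that a component is missing from her training, and the text itself hedges. Part of this stands. Participants may be unaware of which program is expected to do better, and how much the consent information reveals is not shown. It does not rescue the statement that they will not know whether their own program contains cognitive work.

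A reader might infer several stronger points that the document does not support:

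- *The coordinator is unblinded.* The article says "The study coordinator, blinded to group assignment, will enroll eligible female volleyball athletes with DKV and schedule assessments" and also "A study coordinator will send reminder text messages before each scheduled training and assessment session". Reminders plus separate training days show who trains together, not which set is experimental. The article does not state that the two mentions are the same person, and none of the listed tasks measures an outcome.
- *Angles are marked by hand, giving a direct route for rater bias.* The article describes reflective markers and two cameras and does not say how angles are derived.
- *The trial claims double blinding.* It never uses that term. It names the blinded parties and concedes that trainers are not blinded.
- *The bias can be expressed in degrees or standard deviations.* The document gives neither a plausible bias nor a standard deviation for the angle, so any such figure would be invented.

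**Conclusion.** The point holds in this form: the blinding label is wrong as written for participants and is not secured for assessors. The first part follows directly from the two programs as described. The second rests on one strong inference, that the two mentions of the specialist are the same person, and on the absence of any statement separating training oversight from post-test supervision. Whether individual raters would in fact be blinded is left open.

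The size and direction of any bias cannot be derived from the document. What can be said is that the exposure is confined to the post-test, that the explicit route to the primary outcome is the validity judgement on landings together with encouragement during testing, and that the sample size calculation is untouched.

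**What to change.** 1. Reconcile Qualifications of intervention providers, the progression paragraphs under Intervention protocol, and Blinding, so that nobody who oversees, delivers or reviews training conducts or supervises the post-test.
2. Have the two data collectors already named under Data management run the post-test, and state that they take no part in training or progression review.
3. Judge landing validity and derive the angles from video files coded to hide arm and visit.
4. Describe the trial as assessor-blinded only. Acknowledge that participants know the content of their program and may at most be unaware of the hypothesis. Bring the Discussion into line.

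The cost is a reassignment of existing roles, the coding of video files and a less favourable blinding label. Interventions, endpoints and sample size do not change.

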### Theoretical framework and design principles

This intervention protocol was developed based on the seven-step JUMP-ACL framework, incorporating evidence-based neuromuscular and cognitive training principles [18–20]. The intervention aims to address modifiable neuromuscular and biomechanical risk factors associated with ACL injury in young female volleyball athletes through a structured, progressive eight-week program. Previous literature has suggested that female volleyball athletes demonstrating DKV patterns may exhibit altered lower-extremity biomechanics associated with increased ACL loading during high-demand athletic tasks. Accordingly, the intervention is designed to improve movement mechanics and enhance lower-limb neuromuscular control under cognitively demanding conditions that approximate the attentional demands of real-game scenarios.

Based on previous literature regarding barriers to injury prevention program implementation in team sports and practical considerations identified through consultation with volleyball coaches, potential barriers to adherence include limited awareness of injury prevention strategies, time constraints within training schedules, and limited coach training in neuromuscular-cognitive intervention delivery. To address these barriers, the current protocol incorporates several implementation strategies, including comprehensive coach education, integration of training within existing team schedules, provision of detailed instructional materials, and emphasis on the cognitive training component to enhance athlete motivation and engagement.

Before intervention commencement, a two-hour standardized training workshop will be conducted for all participating team coaches and assistant coaches. The workshop will cover ACL injury mechanisms and prevention strategies, neuromuscular and cognitive contributors to injury risk in female athletes, demonstration and hands-on practice of intervention exercises, administration of cognitive tasks and integration of dual-task conditions, use of standardized performance evaluation checklists, identification of movement and cognitive errors, safety procedures, injury management and communication protocols, and strategies to maintain athlete motivation and adherence.

Following the workshop, coaches will be required to achieve a predefined competency threshold of 80% on a practical skills assessment, demonstrating adequate proficiency in exercise instruction, error identification, and progression decision-making.

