### Control group protocol

The control group will receive an active control intervention consisting of the same neuromuscular training exercises as the experimental group but performed exclusively under single-task conditions without cognitive challenges. This design will control for exercise volume, intensity, trainer attention, and social interaction, thereby estimating the additional contribution of cognitive training integration. Training will be delivered three times per week for eight weeks, with each session lasting approximately 60 minutes and following an identical structure to the experimental group: a 15-minute warm-up, 30–40 minutes of main training, and a 10-minute cool-down. Progression will follow the same four-phase structure, with gradual increases in exercise difficulty, intensity, and complexity. Instructional methods will include verbal cueing, demonstration, and corrective feedback; all will be provided with a single-task focus to ensure consistency across groups while eliminating additional cognitive demands.

Both groups will continue their regular volleyball team training sessions, competitions, and usual physical activities throughout the 8-week intervention period. All participants will be instructed to maintain consistent training and competition schedules and report any changes in activity level, injuries, or other relevant health factors.

To enhance motivation and adherence to the eight-week neuromuscular-cognitive training program, each female volleyball player will set an individualized goal based on her personal objectives. These goals will be used to enhance engagement without altering the standardized exercise prescription. A simple checklist will be provided to each participant to track progress, monitor ongoing performance, and record the frequency and type of cognitive and neuromuscular errors, encouraging motivation through ongoing personalized feedback. To avoid mental fatigue and maintain engagement, the protocol includes varied neuromuscular and cognitive training components. Team coaches will actively participate in delivering the training, guiding sessions, and ensuring high-quality execution.

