### Sample size

The sample size was calculated using G*Power software (version 3.1) for a repeated-measures ANOVA (within-between interaction) to detect changes in DKV angle at initial contact. The effect size was derived from the group × time interaction reported for DKV at initial contact in a previous neuromuscular training study with dual cognitive tasks [24] (partial η² = 0.19), converted to an effect size f = 0.48. Based on a significance level (α) of 0.05, statistical power (1-β) of 0.95, and an assumed correlation of r = 0.5 between repeated measures, a minimum total of 18 participants was required. The required sample size was initially determined based on the primary outcome measure (the DKV angle) to ensure sufficient statistical power. To adjust for multiple secondary outcome assessments and an estimated 20% attrition rate, we inflated the target enrollment to 30 participants, who will be randomly allocated in a 1:1 ratio to the intervention and control groups.

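### The control-group section gives every participant a checklist that includes cognitive errors, and nothing restricts or records use of the cognitive drills in regular team practice

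*Protocol article*

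**What the plan says.** Under Control group protocol, controls do the same exercises as the experimental arm, only as single tasks and with no cognitive component. The stated aim is to isolate what cognitive integration adds while holding volume, intensity, trainer attention and social interaction equal.

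The same section then describes individual goals meant to support adherence to the neuromuscular-cognitive program. Every participant receives a checklist on which to "record the frequency and type of cognitive and neuromuscular errors". It also says: "Both groups will continue their regular volleyball team training sessions, competitions, and usual physical activities throughout the 8-week intervention period".

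On delivery, Qualifications of intervention providers states: "Day-to-day implementation of the training program will be conducted by trained team coaches under the supervision of the research team". Under Theoretical framework and design principles, a two-hour workshop for all participating team coaches and assistants covers, among other things, "administration of cognitive tasks and integration of dual-task conditions". Sequence generation randomises individual athletes and describes no stratification or clustering by team.

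Under Blinding, participants are not to know whether their program has a cognitive component. The separation measure given there is: "To minimize communication between groups, intervention and control sessions will be scheduled on separate training days".

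**The concern.** The cognitive tasks are the only intended difference between arms, so anything that carries them, or knowledge of them, to controls acts on the estimand itself. Two features of the text raise this.

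- **The checklist and goals.** The paragraph sits in the control-group section and covers all participants, but its content belongs to the experimental program.
- **The coaches.** The people who can administer the drills are the teams' own coaches. Teammates can fall in opposite arms and still share regular practice. The drills are described as simple and practical, so they could spread easily.

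Exposure of controls would pull the group-by-time interaction towards zero and favour a conclusion of no added benefit. If exposure is not recorded, a null result could not be told apart from a diluted one.

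**Working it through.** **1. The checklist, read both ways.**

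- *It covers controls.* They are to have no cognitive tasks, so they have no cognitive errors to log. A cognitive-error column and goals tied to a neuromuscular-cognitive program then sit badly with the single-task rule. They may also tell a control athlete what the study compares, against the Blinding section.
- *It covers the experimental arm only.* Goal-setting and self-monitoring then differ between arms as well as the cognitive tasks, and the contrast is no longer the cognitive component alone.

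Either way the text needs correcting, and no assumption about leakage is required.

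**2. Routes to controls and what closes them.**

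| Route | Provision | Closed? |
|---|---|---|
| Coach uses drills in a control session | Single-task rule; research-team supervision | Largely |
| Athletes in different arms meet at study sessions | Separate training days | Largely |
| Drills used in regular team practice | No restriction and no specific record | No |

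**3. Effect of leakage on the contrast.** Let E be the effect of the cognitive tasks in experimental sessions and d the effect of drills in shared practice. If effects add, the contrast is (E + d) − d = E, and leakage cancels. It shrinks only if d adds less for athletes already training with dual tasks. The document gives no dose-response, so the shrinkage c is assumed.

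**4. The plan's own sample size.** Inputs from Sample size: "Based on a significance level (α) of 0.05, statistical power (1-β) of 0.95", r = 0.5, and partial η² = 0.19, "converted to an effect size f = 0.48".

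- f = √(0.19/0.81) = 0.484.
- For the within-between interaction with m = 2 times: λ = f²·N·m/(1 − r) = 4f²N, with 1 and N − 2 degrees of freedom.
- With f = 0.48, power is 0.946 at N = 16 and 0.968 at N = 18. The smallest even N reaching 0.95 is 18, as stated.

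**5. Illustration with assumed shrinkage.** f becomes f(1 − c), with f² = 0.19/0.81. Completers: 30 × 0.8 = 24. The second scale, λ = f²N, applies if the cited partial η² already describes the change score. The document does not settle which applies.

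| c | N = 24, λ = 4f²N(1 − c)² | N = 24, λ = f²N(1 − c)² | N = 30, first scale | N = 30, second scale |
|---|---|---|---|---|
| 0 | 99.5% | 62.1% | 99.9% | 72.6% |
| 10% | 98.3% | 53.3% | 99.6% | 63.5% |
| 25% | 92.5% | 39.8% | 97.0% | 48.5% |
| 50% | 62.1% | 20.6% | 72.6% | 24.9% |

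At c = 50% the first scale gives 4 × 0.25 = 1 times f²N, which is the second scale with no leakage. The choice of scale therefore matters as much as halving the contrast. Whatever the scale, the estimated effect shrinks by c, and the sample for equal power grows by about 1/(1 − c)²: 1.23, 1.78 or 4.0.

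**The case against.** The case against a stronger claim is good, and much of it stands.

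- **Who does what.** A reader might infer that the same coach serves both arms and also runs shared practice. The document says neither. It says only that team coaches deliver the program and that athletes continue team training, and it names no coaches by arm. The inference is reasonable but remains an inference.
- **Safeguards.** Study sessions are supervised, Setting places them in the laboratory, control sessions are single-task, and sessions of the two arms fall on separate days. Many tasks also need a prompting partner, cards, cones or Bosu balls. Leakage inside control sessions is therefore unlikely to be large, and it could be seen.
- **Detection.** It would go too far to say that leakage could never come to light. Participants are to report changes in activity, and progression forms are reviewed weekly. Neither, however, asks about cognitive drills in team practice.
- **Other cognitive programs.** The exclusion for structured cognitive training sits in a list that mixes entry and on-study criteria, so it may apply during the trial. It does not clearly reach drills that a team's own coach adds to practice.
- **Cancellation.** Drills in shared practice reach both arms, so they cancel at least in part.
- **Power.** Quoting only the fall from 62% to 21% would import a separate sample-size question. On the protocol's formula, a 25% shrinkage still leaves more than 90% power.
- **Checklist.** The wording may be loose drafting about the experimental arm, and a blank column is not cognitive training. It still has to be reconciled, because that reading leaves goals and self-monitoring unequal between arms.

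One might add that workshop detail belongs in a coach manual, which an article would omit. That answers the absence of operational detail. It does not answer the checklist text, which the article states as it stands.

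**Conclusion.** The point holds in two parts of different strength. The checklist and goal-setting paragraph is inconsistent with the control arm on one reading and adds a second between-arm difference on the other. This follows from the text alone.

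Contamination through team practice is a plausible risk of unknown size, biased towards no added benefit. It rests on the inference that workshop-trained coaches also influence regular practice, and on practice-wide use not cancelling fully between arms. The power figures illustrate assumed shrinkage on two scales and are not estimates of what will happen. The documents do not support saying that the contrast will be diluted, or that the trial is underpowered because of it. The change is worth making because it protects the only contrast in the trial at very little cost.

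**What to change.** 1. In Control group protocol, state that both arms receive the same goal-setting and self-monitoring. Give controls a checklist limited to neuromuscular errors, with goals worded without reference to the cognitive program.
2. In the workshop described under Theoretical framework and design principles, instruct coaches to use the Table 2 cognitive tasks only in experimental-arm sessions until the last post-test is complete.
3. Add one tick-box to the existing standardized forms for any cognitive task used in a control session or in regular team practice, and report it by arm.

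Cost: a second version of the checklist, one instruction and one form item, with no added staff or athletes. The downside is that coaches withhold these drills from team practice until the last post-test.
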